Patient identifiable details (name, date of birth, post code, NHS/CHI number) will be securely sent by each neurosurgery unit to the coordinating centre for consolidation and linkage to the national databases for hospital admissions. These databases are: Hospital Episode Statistics (HES), Patient Episode Database for Wales (PEDW) and Scottish Morbidity Database (SMD). These databases also link to the Civil Registrations—Death and National Registry Scotland for death records. Patients will be linked to hospital admissions based on International Classification of Diseases 10th Revision (ICD-10) diagnosis codes for intracranial haemorrhages and OPCS4 codes for aneurysm occlusion treatments. These databases record every hospital admission in their respective country and thus using this as the outcome source, combined with death records, will allow identification of every aneurysmal subarachnoid haemorrhage (aSAH) regardless of whether they were managed in a neurosurgery unit, a district general hospital, migrated out of the region in which their UIA was diagnosed, or died in the community. The number of patients with aSAH who are not captured by this method, either because they do not present to hospital or emigrate out of the UK, is expected to be very small. Rupture rates can be adjusted based on national emigration rates.

Patients will be censored if there is any occlusive treatment of the UIA or patient death. Occlusive treatment includes either microsurgical or endovascular techniques either partial or complete. If none of these censoring events are observed, then they will be censored on the day the cohort is submitted to the HES/PEDW/SMD databases.

The ICD-10 codes to be searched for rupture events have been selected in accordance with the UK Biobank stroke research and include: aSAH (I60.1-9), intracerebral haemorrhage (I61.0-9), traumatic subarachnoid haemorrhage (S06.6) and spontaneous subdural haemorrhage (I62.00-I62.02).^16^ The use of codes beyond those for aSAH will capture any hospital admissions for aneurysm rupture which have resulted in other forms of intracranial bleed or have been miscoded.

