It is expected that the use of codes beyond that for just aSAH will return many admissions not due to aneurysm rupture. The matched hospital admissions, and death records, will be returned to the coordinating unit who will in turn use pseudonymisation numbers to inform the respective local unit of their patient’s admission for possible aSAH. The local unit will review the imaging studies, discharge summaries and death certificates for these admissions and confirm or refute the diagnosis. Statistical analysis will begin once the diagnosis for all of the matched admissions is confirmed.

The study is currently opening new sites and identifying patients for inclusion. The baseline data collection is planned to finish by 31 July 2023 and the results released no sooner than 31 July 2024. The study end date is currently 31 July 2034 to allow for repeated searching of hospital admissions databases in the future thereby further extending the follow-up period.

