The largest UIA studies are based on Japanese populations and the study with the least bias on a Finnish population. Both observed higher rates of aneurysm rupture than ISUIA. Although it has been assumed ethnicity is a risk factor for rupture and therefore included in the PHASES score, it is not known if the different rupture rates in these studies were due to differences in genetics, environment or study design (and consequently biases). The ROAR study will observe rupture rates in a UK population which removes any concerns over the influence of ethnicity in the results and makes it generalisable for UIA decision making in patients in the UK. Given the use of national-level databases, ROAR is designed as a single country study and as a result there are limitations to its generalisability outside the UK. However, the UK’s population probably more closely resembles most European and North American countries than Japan or Finland.

With the exception of the study by Juvela *et al*,^9^ the follow-up lengths of previous UIA natural history studies are <5 years. Patients are generally not interested in such short-term risks and want to know their lifetime risk. Unfortunately, it is not known if risk is constant over time and therefore if these short-term estimates can be extrapolated to a patient’s lifetime. The hybrid design of the ROAR study will immediately generate follow-up periods of up to 15 years per patient. These will still be shorter than the typical 30-year life expectancy of someone diagnosed with a UIA at 50 and there will still therefore be limitations to extrapolation. However, it will be possible to perform repeat searches of the prospectively maintained databases for hospital admissions and deaths at intervals in the future such that ultimately it will yield realistic lifetime estimates.

Long-term follow-up of such a large cohort of patients is only feasible through the use of national databases. A traditional prospective study would be too costly and time consuming to be realistic as well as suffering significant loss to follow-up. The risk posed by using national databases is that patients emigrating are not censored when they leave the country. However, these databases record when patients deregister their general practice at which time they will be censored from further analysis.

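### The default censoring rule credits a patient whose identifiers fail to link with full rupture-free follow-up, and linkage failure is not among the losses the protocol lists

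*Protocol article*

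**What the plan says.** Under Study design, the units supply the identifiers: "Patient identifiable details (name, date of birth, post code, NHS/CHI number) will be securely sent by each neurosurgery unit". The link is described in terms of events, namely "diagnosis codes for intracranial haemorrhages and OPCS4 codes for aneurysm occlusion treatments", together with death records. On the output side, "The matched hospital admissions, and death records, will be returned to the coordinating unit", after which local units confirm or refute each possible rupture.

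Follow-up ends at occlusive treatment or death. Failing those, "If none of these censoring events are observed, then they will be censored on the day the cohort is submitted".

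The same section says that the method captures every aneurysmal subarachnoid haemorrhage, wherever it was managed. It allows for missed cases on two grounds only: "either because they do not present to hospital or emigrate out of the UK, is expected to be very small". The Discussion adds a further censoring rule, that "these databases record when patients deregister their general practice at which time they will be censored from further analysis". It also says that any available follow-up data from the neurosciences record will be collected, to gauge miscoding.

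**The concern.** An empty return has two possible meanings: the patient was found and had no event, or the patient was never found. Local records go back to 2006 and sit in differing systems at up to 30 units, so some wrong or missing numbers, changed names and old postcodes are plausible. The censoring sentence treats both meanings alike.

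An untraced patient cannot show a rupture, a treatment or a death in the linked data, yet stays at risk until submission. Three results are exposed:

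- **Overall rate.** False event-free years enter the denominator.
- **Objective 1.** An untraced patient who entered at least five years before the search meets the five-year follow-up requirement automatically, as a non-event. PHASES would look more over-predictive, or less under-predictive, than it is.
- **Objective 3.** Traced patients leave the risk set through treatment, death or rupture, while untraced patients do not. The untraced share grows with time and imitates a falling hazard in the plot meant to test whether risk is constant.

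**Working it through.** **The plan's own figures.** Under Sample size, 51 ruptures in 1692 patients over 4.1 years give 51/(1692 × 4.1) = 51/6937.2 = 0.735% a year. Sixty events then need 60/0.00735 = 8161 years, as stated. The implied mean follow-up is 113 905/22 781 = 5.0 years. No linkage rate is stated, so there is no plan figure for the bias itself.

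**Inputs for the bias.**
- From the protocol: rupture rate 0.735% a year; entry from January 2006 to December 2020.
- Assumed: uniform entry; search at mid-2023 (2023.58), when baseline collection is due to end; treatment 2% a year; death 2% a year; unlinked share u = 1, 3 or 5%; failure to link unrelated to rupture risk.

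**Credited follow-up.** Potential follow-up runs from 2.58 to 17.58 years, with mean 10.08. An unlinked patient is credited with all of it. A linked patient leaves at a total rate r = 0.00735 + 0.02 + 0.02 = 0.04735 a year. Averaging (1 − exp(−rt))/r over t from 2.58 to 17.58 gives 7.74 years.

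**Understatement of the overall rate** = 10.08u / [10.08u + 7.74(1 − u)]. **Untraced share of the risk set at year 15** = s = u / [u + (1 − u)exp(−15r)], with exp(−15 × 0.04735) = 0.4915. **Relative fall in the apparent hazard from year 0 to year 15** = 1 − (1 − s)/(1 − u), because the share u is already present at time zero.

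| u | Rate too low by | Untraced share at year 15 | Spurious hazard decline |
|---|---|---|---|
| 1% | 1.3% | 2.0% | 1.0% |
| 3% | 3.9% | 5.9% | 3.0% |
| 5% | 6.4% | 9.7% | 4.9% |

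**Sensitivity to the assumed exits.** With treatment and death combined at 0 to 6% a year, the understatement at u = 5% runs from 5.2% to 7.1%. A simpler check sets the ratio k of unlinked to linked follow-up between 1 and 2, with observed/true rate = (1 − u)/[(1 − u) + uk]. It gives 1.0 to 2.0% at u = 1% and 5.0 to 9.5% at u = 5%.

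**Against sampling error.** 20 000 × 5.0 × 0.00735 = 735 events, so the 95% relative half-width is 1.96/√735 = 7.2%. With the 7.74-year mean above it would be 20 000 × 7.74 × 0.00735 ≈ 1138 events and 5.8%.

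**Objective 1.** Suppose every unlinked patient meets the five-year requirement and a share c of linked, unruptured patients is dropped for early censoring. At u = 5%, the five-year rupture proportion is too low by 5.0% (c = 0), 6.1% (c = 20%) or 7.9% (c = 40%).

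**The case against.** **The document is a condensed article.** Matching rules and the handling of untraced records often sit in a full protocol or data application that is not shown. That they are kept as survivors is inferred from the rule, since the article does not mention them. This stands as a caution, but it does not remove the point. The article fixes the censoring rule, claims complete capture of events, and lists the sources of loss without linkage failure.

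**Not everyone without an event runs to submission.** A reader might infer that linkage returns only event matches and that all other patients count as event-free to submission. The text does not support this. It says that matched records come back, not that nothing else does, and the Discussion also censors at general practice deregistration. That rule is no help to an untraced patient, because deregistration is read from the same databases and needs a successful link.

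**Some missed ruptures could surface.** A reader might infer that the bias is undetectable. A rupture known locally but with no linked episode could appear in the neurosciences follow-up data. The check is partial, is aimed at miscoding, and leaves the censoring rule unchanged.

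**The size is assumed.** This stands. Nothing in the document supports 5% over 1%, and at 1 to 3% the bias lies inside the overall half-width. Calibration by PHASES score is noisier still: 735 events split equally over 11 score groups (an assumption) is about 67 each, or ±24%.

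**Conclusion.** The point holds as a flaw in a stated rule. An untraced patient is credited with full rupture-free follow-up, the direction of bias is always downward, and increasing the sample does not shrink it. The size is unknown because no linkage rate is given. On the assumptions above it is small near 1% unlinked and comparable with the confidence half-width near 5%; the plan as described cannot show which applies.

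A reader might take the 2.0, 5.9 and 9.7% untraced shares at year 15 as the false decline in hazard. They are not: part of each share is there from the start, and the decline is about 1, 3 and 5%.

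**What to change.** 1. Request a trace status (identity matched or not) for every submitted patient from each national database.
2. Apply submission-day censoring only to traced patients, and exclude untraced patients from the primary rupture-rate denominators. Censoring them at their last local contact is not a neutral substitute, since a rupture can itself generate that contact.
3. Report the trace rate by unit and nation, and compare baseline features of traced and untraced patients, because exclusion is unbiased only if failure to link is unrelated to rupture.
4. Add linkage failure to the losses listed under Study design.
5. Reconcile the censoring rules in Study design, Objective 1 and the Discussion, so that deregistration appears wherever time to censoring is defined.

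The cost is a slightly smaller analysed cohort and one more item in each data request. If the first search has already been made, the item can be added to the planned repeat searches.

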### Study setting

This is a multicentre study conducted at up to 30 tertiary neurosurgery units in the UK. Patients will be identified by the neurosurgery unit who diagnosed their UIA. Each unit will collect their baseline data on patients’ clinical and aneurysm characteristics from the time of diagnosis. Central searches of hospital admissions databases, and data analysis, will be performed by the coordinating team at University Hospital Southampton NHS Foundation Trust and the University of Oxford. A separate cohort enriched in patients with autosomal dominant polycystic kidney disease will be established using similar methodology, from up to 70 renal units in the UK.

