### Statistical analysis

#### Objective 1: PHASES validation

The PHASES study provides the coefficients from their Cox regression model and baseline survival at 5 years which allows the absolute 5-year risk of rupture to be calculated for all patients who are not censored before 5 years. Time to censoring will be calculated (whichever is soonest of the date of treatment, date of death or the HES/PEDW/SMD search date) to ensure 5 years of follow-up if rupture has not occurred. Discrimination will be assessed using Harrell’s C-index of concordance and Royston and Sauerbrei’s D statistic. Calibration will be assessed at the 5-year time point using the method by Royston.^19^ These will be used to calculate the number of SAH events per 5 years for each PHASES score (≤2 to 12+) and expressed as a percentage with 95% CI to compare with the PHASES estimates.

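### The article gives three incompatible rules for ending follow-up, and the rule used in the analysis counts time in which no rupture can be recorded as event-free

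*Protocol article*

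**What the plan says.** All references are to the protocol article.

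- **Study design, censoring events:** "Patients will be censored if there is any occlusive treatment of the UIA or patient death".
- **Study design, everyone else:** if neither event is seen, "then they will be censored on the day the cohort is submitted to the HES/PEDW/SMD databases".
- **Objective 1: PHASES validation:** time to censoring is "whichever is soonest of the date of treatment, date of death or the HES/PEDW/SMD search date". Deregistration is not listed. The 5-year risk is then calculated for patients not censored before 5 years.
- **Discussion:** the article names the risk that "patients emigrating are not censored when they leave the country", and answers that "these databases record when patients deregister their general practice at which time they will be censored from further analysis".
- **Study design, on emigration:** "Rupture rates can be adjusted based on national emigration rates". No rate or method is given. The number of ruptures missed, "either because they do not present to hospital or emigrate out of the UK, is expected to be very small".
- **Coverage:** Study setting says "This is a multicentre study conducted at up to 30 tertiary neurosurgery units in the UK", and Study design invites every UK neurosurgery unit. Study design names three admissions databases, each recording admissions in its own country.

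**The concern.** The absolute rupture rate is what this study is meant to deliver, so the denominator matters as much as the event count. A patient should contribute time at risk only while a rupture, had it happened, would have appeared in the linked records.

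Study design and Objective 1 break that principle for emigrants. Outcomes come only from UK admissions and death records, so time abroad can add follow-up but never an event. Take a patient who leaves the country at year 2. Under Objective 1 this patient is a complete 5-year non-event. Under the Discussion the patient is censored at year 2 and leaves the 5-year set. The two rules therefore give different analysis sets and different rates.

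The emigration adjustment makes a third rule. It is needed mainly if emigrants are not censored individually.

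The submission date raises a related problem. It marks an administrative act, not the end of what the data can show. If the extract is complete only to an earlier date, every patient still under observation carries a final stretch of empty follow-up. That stretch falls at the end of each patient's record, so it weighs most on the late part of the cumulative hazard plot, which Objective 3 uses to judge whether risk is constant. The Introduction itself warns that small errors in short-term estimates grow when extrapolated over decades.

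**Working it through.** **1. The plan's own rates.** No stated figure is in dispute, but the base rate is needed. Sample size cites 51 ruptures in 1692 patients over 4.1 years: 51 / (1692 × 4.1) = 51 / 6937.2 = 0.735 per 100 patient-years. Sixty events then need 60/51 × 1692 = 1990.6 patients and 60 / 0.0073517 = 8161 years. The plan states 1990 and 8161, so it reproduces. The feasibility data give 60 / 4010 = 1.50 per 100 patient-years.

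**2. The rules side by side, for a patient who emigrates at year 2.**

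| Source | Follow-up ends | Status at 5 years |
|---|---|---|
| Study design, Objective 1 | submission or search date | non-event, fully followed |
| Discussion | deregistration | censored at year 2 |
| Study design, emigration sentence | not censored; overall rate scaled afterwards | non-event, then corrected in aggregate |

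**3. Emigration under the Study design and Objective 1 rule.** Assume a constant rupture rate λ, a constant emigration rate m and a horizon of T years, and let h = λ + m.

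- Ruptures seen per patient: (λ/h)(1 − e^(−hT)).
- Time counted per patient: T − λ[T/h − (1 − e^(−hT))/h²].

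The documents give no m, so 0.1% to 1% per year is assumed. For λ = 0.00735, m = 0.01 and T = 5, ruptures seen are 0.03521 and time counted is 4.911 years. The observed rate is 0.00717, and 0.00717 / 0.00735 = 0.975, an understatement of 2.5%.

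| Assumed m per year | T = 5 | T = 10 |
|---|---|---|
| 0.1% | 0.3% | 0.5% |
| 1% | 2.5% | 4.9% |

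Using λ = 1.50 per 100 patient-years barely changes these figures. A rough check is mT/2: 0.01 × 5 / 2 = 2.5%.

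**4. Deregistration censoring plus a full national adjustment.** With exact deregistration dates, censoring alone returns the true rate under this model. Adjusting again divides by the ratio from step 3: 1 / 0.9975 = 1.003 and 1 / 0.9753 = 1.025 at 5 years. That is an overstatement of 0.3% to 2.5%, rising to about 0.5% to 5% at 10 years.

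**5. Submission date later than the end of complete data.** Let T be mean observable follow-up among patients reaching that date and L the lag. Events occur only in T but T + L is counted, so the understatement is about L / (T + L). The documents give no L.

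| Assumed L | T = 5 years | T = 10 years |
|---|---|---|
| 1 month | 0.083/5.083 = 1.6% | 0.083/10.083 = 0.8% |
| 3 months | 0.25/5.25 = 4.8% | 0.25/10.25 = 2.4% |
| 6 months | 0.5/5.5 = 9.1% | 0.5/10.5 = 4.8% |

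Five years is the ratio implied by Sample size (113 905 / 22 781 = 5.0), but for the whole cohort. Ten years is closer for patients who reach the search date, if entry is even over 2006 to 2020 and submission is on 31 July 2023, the planned end of baseline collection: follow-up then runs from 2.6 to 17.6 years, mean (2.6 + 17.6)/2 = 10.1.

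**6. Where the lag bites.** Objective 1 needs 5 years of follow-up, so on the same assumptions it draws on about 12.6 years of entry. A 12-month lag affects 1/12.6 = 8% of those patients and costs them on average half a year of five (10%), about 0.8% overall. The late hazard is hit harder. With a 6-month lag, the share of the risk set lying in the empty stretch is 0.5 / (17.6 − 10) = 6.6% at year 10 and 0.5 / (17.6 − 15) = 19% at year 15. In the last six months it is everyone, and the curve is flat by construction.

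**The case against.** The strongest reply is that the Discussion shows what the investigators intend: emigrants are censored at deregistration, and the other two sections simply leave it out. On that reading the emigration bias largely disappears, apart from late or missing deregistrations, and one added phrase settles the matter. This is a fair guess at intent. But Objective 1 is the section an analyst would program from, and its list of end points is closed.

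Four stronger readings are tempting, and the documents do not support them.

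- **That rupture rates will be understated.** The direction depends on the rule followed. Study design and Objective 1 understate; the Discussion rule alone does not; the Discussion rule with a full national adjustment overstates.
- **That the plan corrects twice.** The adjustment is worded as a possibility, and no section says both will be applied. An adjustment confined to emigrants whose deregistration is late or missing would be legitimate.
- **That a coverage lag exists and costs 2% to 9%.** No coverage date or lag is stated, and an extract could be returned well after submission. The upper figures also apply a whole-cohort mean to patients who reach the search date and probably have longer follow-up. Treated and deceased patients dilute the effect further in the overall rate. Later entry, which Study design permits, would push it back up.
- **That patients from an unlinked nation will enter the analysis.** Units are invited, and the count is given only as an upper limit. Nothing says that a unit without linkage will take part, or that its patients would be analysed.

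The objection that the emigration effect is small also stands. The article expects so itself, and the assumed range agrees.

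**Conclusion.** The contradiction is real and lies in the printed text, so it is more than detail left to a fuller document. Three rules for ending follow-up stand side by side, and the one written into the analysis counts unobservable time as event-free.

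The size is modest and rests on assumptions. For emigration it is about 0.3% to 2.5% at 5 years if 0.1% to 1% of patients leave per year: downwards under Study design and Objective 1, upwards by a similar amount if deregistration censoring and a full national adjustment are combined. For the submission date the effect is conditional on a lag that the documents do not give. Lags of 1, 3 or 6 months would mean about 2%, 5% or 9% with 5 years' mean follow-up and about half that with 10, with little effect on Objective 1 and more on the tail of the Objective 3 cumulative hazard. No size is claimed for patients from a nation without linkage. The point is worth correcting because the product is an absolute rate and the correction is nearly free.

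**What to change.** State one rule, in the same words, in Study design, Objective 1 and the Discussion: follow-up ends at the earliest of first occlusive treatment, death, general practice deregistration, or the last date to which the linked admissions and death data are complete. That last date replaces the submission or search date.

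Keep the national emigration adjustment only as a sensitivity analysis, and say what it is for, namely emigrants whose deregistration is late or unrecorded.

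Because every UK unit is invited while three national databases are named, restrict the analysed cohort to patients whose nation has outcome linkage.

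The cost is a few sentences, plus obtaining the completeness date with each extract. If a lag exists, the follow-up given up is time in which no event could have been recorded, so no information on rupture is lost. The same rule can be reused at each planned repeat search.

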### Study design

The Risk of Aneurysm Rupture (ROAR) study is a longitudinal study that uses a hybrid design of patient identification at regional neurosurgical units and prospectively collected national hospital admissions databases for outcome events. The study will establish a cohort of patients with a UIA and measure how many subsequently ruptured. This observed rupture rate can be compared with a rate estimated by the PHASES score to determine its accuracy.

Each neurosurgery unit in the UK will be invited to search their medical records for patients diagnosed with a UIA. This search method will be tailored by the individual neurosurgery unit based on what records they keep, but search strategies may include: multidisciplinary team (MDT) meeting logs, radiology reports or electronic patient records. The search strategy will be predefined by individual units dependent on their record systems. The maximum date range for identifying patients is documents dated 1 January 2006 to 31 December 2020, however, this period may be shorter for each unit depending on availability of records. Whatever date range is chosen by the unit, it will be predefined and if the patient’s UIA was newly diagnosed during this period it will be classed as *new* and those who were diagnosed before this period but identified from a document during the aneurysm follow-up will be classed as *follow-up*, and their recruitment date recorded as the date of the document from which they were identified. This will minimise the prevalence-incidence (Neyman)^14^ selection bias created by identifying patients diagnosed before the unit’s search period but who survive without rupture to make it into the search period, whereas their counterparts diagnosed at the same time who rupture and die are not identified. It will also allow comparison of rupture risk of newly diagnosed aneurysms and those with known diagnoses. Baseline clinical characteristics and aneurysm characteristics will be collected as per the common data elements for UIA research.^15^ All data collectors will undergo training in coding data elements delivered by the coordinating centre. Collecting baseline data from local medical records allows deeper phenotypic typing and higher data fidelity than using national admission databases.

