### Sample size

There are no accepted methods for power calculation for validation studies of prognostic models. Earlier methods included the rule of thumb to have 10 events for every covariate tested, however, more modern methods for minimum sample size calculation have been proposed by Riley *et al.*^17^ The online package *pmsampsize* uses the method by Riley *et al* to estimate the minimum sample size. Using figures from our feasibility work (2124 patients with 60 rupture events over 4010 patient years), estimating 28 df and varying Cox-Snell R^2^ value d from 0.03 to 0.05 resulted in a minimum sample size ranging from 5143 to 8559. The number of df allows for all categorical variables as well as continuous variables such as patient age or aneurysm size which may require polynomial equations.

The method by Riley *et al* is yet to be widely used and does not consider the prevalence of uncommon variables such as ADPKD. The older rule of thumb requiring 10 events per covariate was therefore also considered. For the first objective, the 6 covariates in the PHASES score will be tested suggesting at least 60 SAHs will need to be captured. ISUIA recorded 51 ruptures in 1692 patients over 4.1 years. Sixty events may therefore be expected in 1990 patients with 8161 years of follow-up. For the second objective, 120 events will need to be observed to account for the six additional commonly occurring covariates which would be expected in 3981 patients with 16 332 years of follow-up.

However, the 10 events per covariate rule of thumb does not consider the prevalence of the covariate in the study population. Therefore, rarely occurring populations may have insufficient data to estimate risk. ADPKD is one such population and including it as a covariate requires a larger study size. In ADPKD, 10 events are expected in 1360 patient years of follow-up assuming the risk of SAH is similar to the general population. However, 16 332 years follow-up would only yield 195 years in patients with ADPKD (based on a population study which found 53/4436 patients with UIA had ADPKD).^18^ Therefore, 113 905 years of follow-up would be required to capture 10 ruptures among 1340 years follow-up in patients with ADPKD. This equates to a total cohort of 22 781 patients.

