#### Objective 3: long-term rupture rates

All patients, including those who underwent aneurysm occlusion, will be included in time-to-event analysis which will cover the whole duration of available follow-up. This will include Kaplan-Meier and proportional hazards models for univariate and multivariate survival curve fitting. A cumulative hazard plot will be used to assess if rupture risk is constant or varies with time from diagnosis.

Once the cohort is established, funding will be sought for repeated searches at regular intervals (5 yearly) to update models and provide progressively long-term rupture rates.

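### Follow-up of event-free patients ends on the submission or search day, not on the date to which the returned records are complete; any lag would lower rupture rates and make a constant hazard seem to fall

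*Protocol article*

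**What the plan says.** The protocol article fixes the end of follow-up in two places.

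- Study design: patients are censored at occlusive treatment or death. If neither occurs, "then they will be censored on the day the cohort is submitted to the HES/PEDW/SMD databases".
- Objective 1: time to censoring is "whichever is soonest of the date of treatment, date of death or the HES/PEDW/SMD search date". This date is used to make sure that a patient without rupture has 5 years of follow-up.

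On the outcome source, Study design says "These databases record every hospital admission in their respective country". It gives no date to which an extract is complete and no recording delay. Objective 3 covers the whole of available follow-up and states: "A cumulative hazard plot will be used to assess if rupture risk is constant or varies with time from diagnosis".

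**The concern.** A patient should count as at risk only while an event, had it happened, would have been seen. Here a rupture is seen only after an admission has been coded and has reached a national database, or a death has been registered. The day the cohort is submitted is an event in the study's own calendar. Nothing in the article links it to the last day those sources cover.

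If coverage ends before that day, three things follow:

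- Ruptures in the gap leave the numerator, while the person-time stays in the denominator. Treatments and deaths in the gap are missed too, which adds a little more false time at risk.
- The gap sits at the end of each patient's follow-up. Because entry is staggered, it takes a growing share of the risk set as time from diagnosis increases. A constant hazard would then look as if it falls, which is what Objective 3 is meant to judge.
- Some patients would pass the 5-year check in Objective 1 with less than 5 observed years.

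The local review of imaging and records does not repair this, because it examines only matches that were returned.

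**Working it through.** **Inputs from the protocol article**

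- Planning rupture rate, from "ISUIA recorded 51 ruptures in 1692 patients over 4.1 years": h = 51 / (1692 × 4.1) = 51 / 6937.2 = 0.00735 per patient-year.
- Higher rate, from the feasibility work ("2124 patients with 60 rupture events over 4010 patient years"): 60 / 4010 = 0.01496 per patient-year.
- Entry window: "The maximum date range for identifying patients is documents dated 1 January 2006 to 31 December 2020".
- Earliest plausible submission: "The baseline data collection is planned to finish by 31 July 2023".
- Target cohort: 20 000.

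**Assumptions (not in the article)**

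Entry is uniform over the 15 years, the true hazard is constant, and submission is on 31 July 2023. The lag L is 0, 1, 3, 6 or 12 months. Other exits are 0 or 3% a year.

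**Reproducing the plan's own figure**

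60 / 51 × 1692 = 1990.6 patients, and 1990.6 × 4.1 = 8161 years. The Sample size section states 1990 and 8161, so the rate is read as the authors used it.

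**Why the deficit grows with time**

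Potential follow-up F runs from 2.58 to 17.58 years. At time t from diagnosis, the patients counted at risk have F > t, but an event can be seen only if F > t + L. For t above 2.58, ignoring exits inside the gap,

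observed / true hazard ≈ (17.58 − t − L) / (17.58 − t).

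Over years 10 to 13 the average of 17.58 − t is 17.58 − 11.5 = 6.08, so the ratio is 1 − L / 6.08. This gives 0.986, 0.959, 0.918 and 0.836 for 1, 3, 6 and 12 months.

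**Numerical results (0.735% a year, no other exits)**

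| Assumed lag (months) | 0 | 1 | 3 | 6 | 12 |
|---|---|---|---|---|---|
| Overall rate, observed/true | 1.00 | 0.992 | 0.976 | 0.952 | 0.903 |
| Hazard, years 2–5 | 1.00 | 0.995 | 0.985 | 0.968 | 0.933 |
| Hazard, years 5–10 | 1.00 | 0.992 | 0.975 | 0.950 | 0.901 |
| Hazard, years 10–15 | 1.00 | 0.984 | 0.951 | 0.902 | 0.803 |
| Hazard, years 13–17 | 1.00 | 0.97 | 0.90 | 0.81 | 0.62 |
| Kaplan–Meier-type risk at 5 years (%) | 3.61 | 3.60 | 3.58 | 3.54 | 3.46 |
| Same at 10 years (%) | 7.09 | 7.05 | 6.97 | 6.85 | 6.60 |
| Same at 15 years (%) | 10.44 | 10.35 | 10.15 | 9.85 | 9.25 |

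In years 0 to 2 the ratio is 1.00 at every lag. With 3% a year of other exits the overall ratios are 0.993, 0.979, 0.957 and 0.912. With 20% treated early and 2% a year dying they are 0.993, 0.978, 0.956 and 0.910. Moving submission to July 2024 leaves the overall ratio at 0.99 for 1 month and between 0.90 and 0.92 for 12 months.

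**Ruptures not returned**

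The count is 20 000 × share still at risk × L × h. With 60% at risk it is about 7, 22, 44 and 88 for lags of 1, 3, 6 and 12 months. With 80% at risk it is about 10, 29, 59 and 118. At the higher feasibility rate and 80% at risk it is about 20, 60, 120 and 239.

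**The 5-year check**

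The share with 5 nominal but not 5 observed years is L / 15: 0.6, 1.7, 3.3 and 6.7%. Of 20 000 patients that is about 110, 330, 670 and 1330, before other exits.

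**The case against.** The strongest reply is that no lag is documented. Submission comes first and the matched records are returned later, and the article does not say when the extract is cut. If the extract is complete to the submission day, that day is a valid censoring date and the bias is zero. This stands. A reader might infer that recent ruptures are certainly missed, or that three admissions databases and separate death registers cannot all be complete to one day. The article shows neither.

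A reader might also infer that the two sections contradict each other. They need not: submitting the cohort is how the search is run, so the submission day and the search date can be the same event under two names. What stands is that the terms differ and that neither refers to coverage.

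The size can be challenged too. With 20% treated early and 2% a year dying, about 1000 ruptures are expected, so sampling error on the overall rate is about 1.96 / √1000 = ±6%. Only the 12-month lag exceeds that. Years 13 to 17 would hold about 55 ruptures, or roughly 1.96 / √55 = ±26%, so the deficits there at lags up to 6 months would be hard to see. Units may also search shorter windows than 2006 to 2020, which thins that tail further. All this is fair, but sampling error does not excuse a systematic error that runs in one direction.

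Finally, follow-up data from neurosciences records (Discussion) may catch some ruptures, and repeat searches would recover those missed at the first. These help only in part. The records are collected to measure miscoding, the repeat searches depend on funding, and each new search under the same rule would have its own gap at the end.

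**Conclusion.** The concern holds conditionally. The article states a censoring date, and that date is not tied to data coverage. Where coverage ends before it, rates are understated and a constant hazard appears to decline. For assumed lags of 0, 1, 3, 6 and 12 months:

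- the overall rate is understated by about 0, 1, 2, 4 to 5 and 9 to 10%;
- the hazard in years 10 to 13 is understated by about 0, 1, 4, 8 and 16 to 17%.

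The 5-year risk changes by at most about 0.15 percentage points, so the comparison with PHASES is little affected. Deficits above about 20% arise only with long assumed lags in the sparse tail beyond about 13 years.

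These sizes rest on uniform entry, a constant true hazard, submission in mid-2023 and a lag that the article does not give. Confidence is moderate. This is a worthwhile low-cost correction, mainly to protect Objective 3, and not a defect that must be cured before the study can proceed.

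**What to change.** Use one identical sentence in Study design and Objective 1. For each nation, the administrative censoring date is the earliest of the submission date, the date to which that nation's admission data are complete, and the date to which its death data are complete. Count no events and no person-time after it. Apply the same date to the 5-year follow-up check, to Objective 3 and at each repeat search, and report the dates with the results.

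The cost is one sentence plus the coverage dates for each extract. If there is a lag, a few months of nominal follow-up per patient are given up. If there is none, nothing is lost.
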